# Does propolis affect the quality of life and complications in subjects with irritable bowel syndrome (diagnosed with Rome IV criteria)? A study protocol of the randomized, double-blinded, placebo-controlled clinical trial

**DOI:** 10.1186/s13063-020-04615-5

**Published:** 2020-08-05

**Keywords:** Gastrointestinal diseases, Irritable bowel syndrome, Propolis, Anti-inflammatory agent

## Abstract

**Background:**

Irritable bowel syndrome (IBS) is one of the most frequent and recurrent gastrointestinal diseases. However, up to now, no pharmacological agent has been approved to treat IBS. Emerging evidence showed that inflammation has a vital role in enhancing nervous system sensitivity and perception of abdominal pain in subjects with IBS. Propolis is an herbal substance with a broad spectrum of antioxidants, anti-inflammatory, and prebiotic properties, which might exert beneficial effects to reduce the severity of IBS. The current clinical trial aims to evaluate the efficacy of propolis supplementation on IBS.

**Methods:**

This single-center, randomized, double-blind, placebo-controlled clinical trial will be performed to evaluate the effect of propolis supplementation in adult patients with IBS diagnosed with Rome IV criteria. Fifty-two eligible patients will randomly be allocated to receive a propolis tablet (450 mg, containing 100 mg polyphenol compounds) or identical placebo, twice daily for 6 weeks. The primary outcome of the trial is an improvement in IBS severity from baseline to the sixth week of intervention. The secondary outcomes include the change in weight, waist circumference, and IBS quality of life. We will use the paired sample *t* test or Mann-Whitney *U* test for the within-group comparison and independent sample *t* test or Wilcoxon rank-sum and chi-square test or Fisher’s exact test for the between-group comparison. Besides, a multivariable-adjusted mean effect will be computed using the ANCOVA test.

**Discussion:**

We hypothesize that propolis supplementation would be useful for treating IBS through its antioxidants, anti-inflammatory, and prebiotic properties. This trial will show the results of propolis supplementation, whether positive or negative, on IBS. If the current trial confirms our hypothesis, propolis supplementation can be a new choice in adjunctive therapy of IBS.

**Trial registration:**

Iranian Registry of Clinical Trials IRCT20190708044154N1. Registered on 26 December 2019. Updated on 13 February 2020. https://en.irct.ir/trial/40983

## Background

Irritable bowel syndrome (IBS) is one of the most common and recurrent gastrointestinal (GI) diseases with unexplained abdominal discomfort and bowel habit changes [1]. There has been no documentation of structural bowel dysfunction or metabolic disorders in patients with IBS, and diagnosis is made based on the Rome IV criteria as the latest and newest diagnostic tool for IBS [2, 3]. According to the Bristol Stool Form Scale (BSFS), IBS is classified into diarrhea-predominant (IBS-D), constipation-predominant (IBS-C), and mixed form (IBS-M). This functional bowel disease affects approximately 10% of the general population [4].

To date, the exact pathogenic mechanisms of IBS have not been completely clarified. However, several factors are expected to play a role in IBS etiology, including microscopic inflammation, enhancement of GI tract permeability, alterations of the nervous system (such as abnormal GI motility and visceral hypersensitivity), chronic infections, genetics, psychosocial stress, changes in brain-gut axis, and also alterations of gut flora [5–8]. Besides, oxidative stress and inflammation have a role in the augmentation of abdominal pain perception and nervous system sensitivity in these patients [8]. Various therapeutic approaches to IBS treatment have been suggested due to possible pathogenic mechanisms. However, up to now, no pharmacological agent has been approved to treat all IBS symptoms or all IBS forms [9]. Recent clinical evidence indicates that prebiotics and probiotics might improve the IBS symptoms severity through modulating the mucosal immune response [10, 11]. Furthermore, some plant metabolites, such as polyphenol compounds, have been shown to maintain GI function and the body’s health due to gut-microbiota modulation and their anti-inflammatory and antioxidant properties [12, 13].

Propolis, a natural resin, is produced by bees from petals and plant buds. It is a complex substance mainly made up of polyphenol compounds and terpenes, with a broad spectrum of antioxidants, anti-inflammatory, and prebiotic properties [14]. Recent evidence indicates that the administration of propolis reduces the histopathological scores of colon damage, increases the mucin levels, and suppresses colonic inflammation in colitis animals [15–17]. In rats with obstructive jaundice, propolis exerts protective effects against intestinal villus atrophy and bacterial translocation [18]. Moreover, some studies showed that propolis increases the secretion of mucin and mucosal prostaglandin E_2_ levels [19], modulates gut microbiota, and reduces the levels of circulating endotoxin and expression of toll-like receptor gene in animals [20]. Further efforts in this area also showed that propolis could improve the intestinal barrier function through the upregulation of the intestinal tight junction proteins gene [21].

### Study rationale

Considering to the tight relationship between inflammation, oxidative stress, dysbiosis of the gut microbiota, and alteration in the intestinal permeability with IBS, it seems that propolis supplementation would contribute to improve the health of the gastrointestinal system in patients with IBS. Most clinical trials reported the safety and efficacy of propolis supplementation on glycemic control in patients with type 2 diabetes mellitus [22]. To the best of our knowledge, there is no clinical trial investigating the effect of propolis in patients with IBS.

### Objectives

The current clinical trial aims to evaluate the effect of propolis supplementation on the IBS Severity Index (IBSSI). Also, secondary objectives of this trial include the changes in weight, body mass index (BMI), waist circumference (WC), IBS quality of life (IBS-QOL), and anxiety with propolis supplementation compared to placebo. For controlling of confounder factors, changes in dietary intakes, physical activity levels, and anxiety will be assessed in the current trial.

## Materials and methods

### Study design

The current study is a prospective, single-center, randomized, double-blind, placebo-controlled clinical trial evaluating the efficacy of propolis supplementation in subjects with IBS. This clinical trial will be performed at the gastrointestinal clinic, a referral center for gastrointestinal diseases in Ahvaz, the southwest of Iran. All volunteers will provide written informed consent before participation in this randomized clinical trial.

The current trial is registered at the Iranian Registry of Clinical (ID: IRCT20190708044154N1). The study protocol was drafted and developed in accordance with the Standard Protocol Items: Recommendations for Interventional Trials (SPIRIT) 2013 checklist (Additional file 1). The protocol flow chart and timeline of the study are shown in Fig. 1 and Table 1, respectively. A protocol deviation is accidental and unintentional changes to the study protocol which have no significant impact on the study’s risk or benefit, subject’s rights, safety or welfare, and the integrity of the data [23]. The protocol deviations may result from the action of the patients or researchers. Examples of the protocol deviation for this study include:
A rescheduled study visitFailure to collect an ancillary self-report questionnaireSubject’s refusal to complete scheduled research activities.

**Fig. 1 Fig1:**
[figure not shown]
Study flow chart of enrolment, allocation, intervention, and assessment

**Table 1 Tab1:** Timeline of the trial

Explanation of the trial activities	Time (month)											
	1	2	3	4	5	6	7	8	9	10	11	12
Material preparation	*	*	*	*	*							
Recruitment						*	*					
Intervention								*				
Data analysis									*	*		
Writing the final report of the trial											*	*
The expected time	*	*	*	*	*	*	*	*	*	*	*	*

Any amendments of this study protocol which have related to safety and benefit of participants will need to be agreed upon by Department of Clinical Nutrition in Tabriz University of Medical Sciences and approved by the Medical Ethics Committee of Tabriz University of Medical Sciences, Tabriz, Iran, before the implementation of the study. Any change in the study protocol will be sent to Trial Journal (www.trialsjournal.biomedcentral.com).

### Study setting

This clinical trial will be performed at the gastrointestinal clinic, a referral center for gastrointestinal diseases in Ahvaz, the southwest of Iran. All participants will be informed of this study through advertisements on the clinic’s television.

### Study participants and recruitment

Volunteers will be recruited from outpatients referred to the gastrointestinal clinic in Ahvaz, Iran, through advertisement on the clinic’s television. Patients who meet the international *Rome IV* criteria for diagnosing IBS will be assessed for eligibility criteria, after differentiating IBS from structural bowel disorders by an expert gastroenterologist ([name]) at this clinic. The international *Rome IV diagnostic Questionnaire* is the well-known and latest diagnostic instrument in the field of IBS in clinical researches. According to *Rome IV* criteria, individual who had recurrent abdominal pain or discomfort at least 1 day/week in the last 3 months with symptom onset at least 6 months before a diagnosis has IBS if she/he had at least two of the following criteria: symptom improvement with defecation, onset simultaneous with a change in the frequency, or/and onset simultaneous with a change in the form or appearance [3].

### Inclusion criteria

The inclusion criteria will consist of patients who have an age between 18 and 65 years, who have an IBS-C or IBS-M (much more common forms of IBS) according to the BSFS, and who fill out a written informed consent to participation in this trial.

### Exclusion criteria

The exclusion criteria will consist of patients who are a pregnant or breastfeeding, who have/had a malignancy or other chronic digestive diseases such as IBD, who have regular use of drugs that modify GI movements (such as metoclopramide, cisapride, narcotics, and diphenoxylate), who have regular use of laxatives or antibiotics, who have regular use of the prebiotic or probiotic supplement, who have regular use of antidepressant drugs, who have a history of major surgery in the gastrointestinal tract (Billroth’s operation, having an ostomy and any resection of any part of the digestive tract), who underwent psychotherapy, who have a restricted diet (such as vegetarian diets), and who have/had an allergy to bee products.

Participants who are unwilling to continue collaborating on the study, have the sensitivity to propolis supplement, become pregnant, alter the patient’s disease to other gastrointestinal diseases, or have poor compliance with the assigned treatment (less than 80%) will be withdrawn from follow-up.

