### Sample size calculation

We used Hern’s single-stage phase II methodology to calculate the sample size [34]. Based on results from other dietary supplements in patients with IBS [35] in which 15% of patients in the placebo group (*P*_0_) and 40% of patients in the intervention group (*P*_*1*_) had complete remission from symptoms of IBS, we need 22 patients in each trial group with a power of 80%. To compensate for withdrawal during follow-up, we increase the final sample size by 20%, to 26 patients in each group.

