### Safety evaluation

In this study, the dose of propolis supplementation was extrapolated from the study conducted by Sabuncuoglu et al. [18] in which the administration of propolis at a dose of 100 mg kg^−1^ improves the function of the GI tract and gut microbiota in rats. Based on the following formula for the conversion of animal dose to human [36] and reference body weight of 60 kg, the dose of propolis for a human is approximately 900 mg. At this dose of propolis, no adverse events were reported in the previous clinical trials.
$$ {\displaystyle \begin{array}{c}\mathrm{Human}\ \mathrm{equivalent}\ \mathrm{dose}\ \left(\mathrm{mg}/\mathrm{kg}\right)=\mathrm{Animal}\ \mathrm{dose}\left(\mathrm{mg}/\mathrm{kg}\right)\times \left({\mathrm{km}}_{\mathrm{Animal}}/{\mathrm{km}}_{\mathrm{Human}}\right)\\ {}\mathrm{Animal}\ \mathrm{dose}=100\ \mathrm{mg}/\mathrm{kg}\kern0.5em {\mathrm{km}}_{\mathrm{rat}}=6\kern0.5em {\mathrm{km}}_{\mathrm{Human}}=37\end{array}} $$

Patients will be asked to avoid taking the assigned supplement following the occurrence of adverse events and to immediately call the study physician or other investigators. One of the study researchers will be instructed to call the participants weekly by phone and ask them about experiencing any adverse events. Tabriz University of Medical Sciences is responsible to follow up on any adverse events and reports them to the Medical Ethics Committee of Tabriz University of Medical Sciences for decision making. If the reported adverse events are related to the consumed supplements, the study will be stopped and patients will be referred to a specialist for immediate treatment in which can be treated free of charge. Participants who are unwilling to continue collaborating on the study will be able to discontinue the trial at any time.

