### Data management

One of the researchers will check the coding, security, and storage of data. Also, she/he will check data entry, and data values double times. If any patient reports the occurrence of adverse events, more information is needed for the decision making about excluding the patient from the study.According to the Medical Ethics Committee Criteria, unblinding is permissible in this situation, and we can specify whether the patient has received the propolis or placebo.

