### Adherence to the intervention

All patients will be instructed on how to use their supplements at the baseline, each phone call, and intermediate visits (t_3_). All patients will be asked to complete a daily calendar immediately after consumption of their assigned treatments. The adherence to intervention refers to the degree to which the behavior of trial participants corresponds to the intervention assigned to them. Adherence to the assigned treatments will be checked by means of a daily calendar at each phone call and will be rechecked by counting the returned tablets at the end of the trial (t_7_). Compliance will be calculated based on the following formula:
$$ \mathrm{Compliance}\ \mathrm{rate}:\left(\mathrm{Tablets}\ \mathrm{taken}/\mathrm{Tablets}\ \mathrm{prescribed}\right)\times 100 $$

The compliance less than 80% will be classified as poor compliance [37].

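### Sensitivity to the supplement or compliance below 80% ends follow-up, not only treatment, so week-6 IBSSI scores that the intention-to-treat analysis needs may go uncollected

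*Protocol article*

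**What the plan says.** The second paragraph of Exclusion criteria concerns patients already in the trial. It removes those who "have the sensitivity to propolis supplement" and those with "poor compliance with the assigned treatment (less than 80%) will be withdrawn from follow-up". Unwillingness to continue, pregnancy and a change to another gastrointestinal disease are in the same list. What ends is follow-up, not the tablets.

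Other sections bear on this:

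- Outcomes: the primary outcome is the change in IBS severity from baseline to week 6.
- Statistical analysis: intention to treat is the primary approach. Missing values are to be completed by a multiple imputation method chosen according to the missing-data pattern.
- Adherence to the intervention: a daily calendar is checked at each phone call, and adherence "will be rechecked by counting the returned tablets at the end of the trial" (t7).
- Safety evaluation: "Patients will be asked to avoid taking the assigned supplement following the occurrence of adverse events and to immediately call the study physician" or another investigator.
- Data management: after an adverse event, "more information is needed for the decision making about excluding the patient from the study", and "unblinding is permissible in this situation, and we can specify whether the patient has received the propolis or placebo".
- Sample size calculation: "To compensate for withdrawal during follow-up, we increase the final sample size by 20" per cent, from 22 to 26 per group.

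No section says that a patient withdrawn under these rules is still assessed at week 6.

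**The concern.** An intention-to-treat analysis needs the outcome of every randomised patient, whether or not the tablets were taken. A rule that closes follow-up because of intolerance or low adherence discards that outcome by design. The analysis must then model a score that one more visit could have supplied.

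The reasons for the loss are not neutral. Sensitivity to propolis may arise mainly in the propolis arm, and poor compliance may reflect how the patient feels. Patients lost this way may therefore differ from retained patients in ways that the observed data do not explain. Imputation under missing at random would then give a biased treatment difference.

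A related but weaker point lies in Data management. It allows a case-by-case decision to exclude a patient after an adverse event, possibly with the arm known, and does not say whether outcomes are still collected.

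**Working it through.** **1. The plan's own allowance.** The 22 per group is reproduced by an exact single-stage, single-arm binomial design with p0 = 0.15, p1 = 0.40, one-sided alpha of at most 0.05 and power of at least 0.80. The smallest n is 22, with an exact alpha of 0.037 and power of 0.842. Then 22 × 1.2 = 26.4, taken as 26. The allowance is 26 − 22 = 4 per arm, or 4/26 = 15.4%, and covers withdrawal for any reason. It is not an estimate for sensitivity or poor compliance.

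**2. When the compliance rule would cost the score.** Two tablets a day for 42 days is 84 tablets.

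- If the denominator is the full course, 16 missed gives 68/84 = 81.0% (kept) and 17 missed gives 67/84 = 79.8% (withdrawn).
- A patient who stops for good after day 28 misses the 17th tablet on day 37 (17/2 = 8.5 days later), before the end of week 6. Scattered misses may not add up to 17 until t7, when the week-6 outcome is due anyway.
- If the denominator is tablets due so far, 14 are due by the first weekly call, and 3 missed gives 11/14 = 78.6%.

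The article does not say which denominator applies, or that a weekly calendar check triggers withdrawal. The score is lost only if withdrawal precedes t7. The sensitivity clause does not depend on the tablet count.

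**3. Size on the IBSSI scale (illustration only).** Let k patients of 26 be withdrawn in one arm. Let D be their mean week-6 change minus that of the retained patients; a higher IBSSI is worse. If imputation merely reproduces the retained mean, the arm mean is wrong by (k/26) × D. No document gives a value for D, so a range is assumed.

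| k | D = 25 | D = 50 | D = 100 |
|---|---|---|---|
| 1 | 1.0 | 1.9 | 3.8 |
| 4 | 3.8 | 7.7 | 15.4 |

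With losses in the propolis arm only, the effect is overstated if those lost did worse (D > 0). It is understated by the same amount if they did better (D < 0), for example because they stopped tablets once well. With losses in both arms, the error in the difference depends on (k × D for propolis − k × D for placebo)/26, so similar losses partly cancel.

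**4. The same on the planning scale.** The sample size rates are complete remission of 40% against 15%, which is not the primary outcome. With k lost from the propolis arm only and a remission rate r among them, the apparent propolis rate is (26 × 0.40 − r × k)/(26 − k).

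- r = 0: 10.4/25 = 41.6% (k = 1); 10.4/22 = 47.3% (k = 4).
- r = 0.2: 10.2/25 = 40.8%; 9.6/22 = 43.6%.
- r = 0.4: 40.0% for any k, so no bias.
- r = 0.6: 9.8/25 = 39.2%; 8.0/22 = 36.4%.

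Against 15%, the true 25-point difference would appear as anything from 21.4 to 32.3 points. The upper end is an extreme: the whole allowance lost from one arm, with no remitters among those lost.

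**The case against.** The strongest defence is that few patients may be affected and that the plan already handles them.

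- People who have or had an allergy to bee products are excluded at entry, which shrinks the sensitivity route. On earlier trials the article states: "At this dose of propolis, no adverse events were reported in the previous clinical trials". Both points stand and limit the expected number of cases, although neither says anything about poor compliance.
- Intention to treat is primary, multiple imputation is planned, a linear mixed model is a possible substitute, and retention measures are listed. A reader might infer that withdrawn patients drop out of the analysis. The documents do not support that, because imputation keeps them in. What remains is narrower: missing data that could be avoided are modelled, usually under missing at random, when the reasons for loss make that doubtful.
- Low compliance may be established only by the tablet count at t7. A reader might infer that every patient below 80% loses the week-6 score. The documents do not settle the timing, so this cannot be claimed.
- A reader might also infer that patients with adverse events are withdrawn from follow-up, or excluded according to arm. Data management describes only a case-by-case decision, and unblinding after an adverse event is a common safety provision. Nothing says that the arm decides the outcome.
- Safety evaluation says the study stops if adverse events are related to the supplement. Whether this means the trial or the patient, it does not say that the week-6 score is kept.

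The point is not one to leave to a statistical analysis plan, which cannot recover scores that the protocol's withdrawal rule prevented from being collected.

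**Conclusion.** The concern holds for the withdrawal rule in Exclusion criteria. For sensitivity, and for compliance below 80% acted on before t7, a stated rule ends collection of the primary outcome and works against the intention-to-treat analysis. The adverse-event provision in Data management is secondary: an ambiguity about outcome collection, not a follow-up rule.

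The frequency, direction and size of any bias are unknown. The illustrations assume losses in one arm, imputation that copies the retained patients and values of D with no source; four losses is the allowance for all withdrawals. One loss shifts an arm's mean IBSSI by about 1 to 4 points, and four losses by about 4 to 15, in either direction. A reader might infer that the propolis effect will be overstated, but the documents do not support a direction. The case for change rests on the avoidable conflict and the low cost of removing it. Confidence is medium.

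**What to change.** In Exclusion criteria, state that sensitivity to the supplement or compliance below 80% ends study treatment at most. Unless consent is withdrawn, the patient stays in follow-up, has the week-6 IBSSI collected and is analysed in the randomised arm. Apply the same wording in Data management to any exclusion after an adverse event. Use the 80% threshold only to define a secondary per-protocol analysis.

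The cost is a wording change in two sections and a week-6 visit for patients who are off tablets. The number randomised does not change. Including patients with less exposure may make the estimated effect slightly smaller, which is consistent with what an intention-to-treat analysis is meant to estimate.
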